### Procedures

All Institutional Review Boards (UCLA, UC Davis, University of Rochester, University of Kansas, University of Pennsylvania, Drexel University, and University of Washington) approved this study. Recruitment for MTG in agencies and RR and SDMLI in schools will include an informational email and video about the study and respective intervention and UNITED implementation strategy. If agencies/schools are interested, we then meet with agency leaders/directors or school administrators via videoconference to inform them about the study, participation requirements, and answer any questions (approximately 30 min). Following approval by the agency lead/director or school administrator, we will meet with agency staff or teachers/school staff to obtain their consent to participate in the study. Subsequently, we will ask agency staff or teachers/school staff from each respective intervention to send recruitment materials home to parents/caregivers of autistic individuals under 16 years of age. Recruitment materials explain what is expected of research participants and detail all research activities. If interested, parents/caregivers contact the research team to complete informed consent.

To test UNITED, we will randomize half of the community study sites (agencies for MTG and public schools for RR and SDLMI) to UNITED, and the other half to IAU. We will collect SNA for sites in both study arms. The SNA questions will include identification of agency/school staff to use the EBI and/or provide implementation support. See Measures and Table 2. Randomization will be conducted via a customized system tailored for the research design. The system will make a treatment assignment only if the participating agencies/schools meet study criteria. All randomizations will be further stratified using a minimization allocation method. MTG randomization of agencies will be stratified on the number of peer navigators within the agency (peer navigator ≤ 2 vs. > 2) to ensure that treatment groups are balanced for variables that may correlate highly with outcomes. RR randomization of school teams will be stratified on two baseline measures: (a) number of school personnel who will learn and deliver Remaking Recess (school personnel ≤ 2 vs. > 2), and (b) number of children with ASD/NDD in the school (number of children with ASD/NDD ≤ 2 vs. > 2). SDLMI randomization of school teams will occur within each CRE and will be further stratified on two baseline measures: (a) number of school personnel who will learn and deliver SDLMI (school personnel ≤ 2 vs. > 2); and (b) type of school (middle vs high school).

**Table 2 Tab2:** Social network questions on the roster questionnaire and the social network survey

Roster Questionnaire (Baseline/T2/T3)				
Q#	Network Question	MTG specific language	RR specific language	SDLMI specific language
1	Name the people who can do the (MTG/RR/SDLMI) intervention at your organization. Please name as many as you can think of.	For example, parents who have older children with disabilities who would be good mentors for parents just learning about their child’s disability.	For example, playground monitors who support inclusion for students with disabilities during recess. Please name as many as you can think of.	For example, special education teachers who support students with disabilities to achieve their goals.
2	Name the people at your organization or outside your organization who can provide implementation support to your staff who are doing the (MTG/RR/SDLMI) intervention. Please name as many as you can think of.	For example, staff who could providing coaching or resource coordination for staff who are doing the intervention with caregivers.	For example, disability specialists, special education teachers, behavioral specialist who could provide coaching or resource coordination. Please name as many as you can think of.	For example, disability specialists, school counselors and behavioral specialist who could provide coaching or resource coordination.
3	Name the people who can make financial decisions for funding the (MTG/RR/SDLMI) intervention at your agency. Please name as many as you can think of.	For example, organizational leaders or administrators.	For example, principals or district leaders.	or example, principals or district leaders
Social Network Survey (Baseline)				
Q#	Network Question	MTG specific language	RR specific language	SDLMI specific language
1	Name the best people at your agency for doing interventions that …	…connect caregivers of child with disabilities to services for the first time post diagnosis. For example, please name parents affiliated with or employed at your agency who have older children with disabilities who would be good mentors for parents just learning about their child’s disability.	…support the social engagement of children with disabilities during recess at your school. For example, staff who are skilled at helping students with disabilities engage with their peers during recess.	… support goal setting and self-determination for students with disabilities For example, special education teachers who are skilled at helping their students with disabilities make goals and achieve them.
2	Name the best people at your agency to support the implementation of interventions that…	…connect caregivers of child with disabilities to services for the first time post diagnosis. For example, please name staff who are skilled at providing support, training, mentorship, resource coordination or agency leadership for the parents who are doing the intervention with caregivers.	…support the social engagement of children with disabilities during recess at your school. For example, staff who are skilled at provide support, training, mentorship, resource coordination or school leadership for staff who are doing recess intervention with students with disabilities.	…support goal setting and self-determination for students with disabilities. For example, staff who are skilled at providing support, training, mentorship, resource coordination or school leadership for staff who are doing the intervention with students.
3	Name the best people at your agency for making financial decisions to support funding for interventions that…	…connect caregivers of child with disabilities to services for the first time post diagnosis. For example, agency leaders, financial directors or organizational administrators who are skilled at securing funding for interventions that support caregivers to connect their children with disabilities to services for the first time post diagnosis.	…support the social engagement of children with disabilities during recess at your school For example, school leaders, financial directors or district administrators who are skilled at securing funding for interventions that support recess intervention for students with disabilities.	…support goal setting and self-determination for students with disabilities. For example, school leaders, financial directors or district administrators who are skilled at securing funding for interventions that support goal setting and self-determination for students with disabilities at your school.
4	Name all the people at your agency you collaborated with during the past year to support interventions for…	…connect caregivers of child with disabilities to services for the first time post diagnosis.	…support the social engagement of children with disabilities during recess at your school.	…support goal setting and self-determination for students with disabilities.
4	Collaborators can include: -people you worked with to provide the intervention -people who provided encouragement, training or guidance about the intervention -People who provided resources needed to do the interventions -people who worked with you to support staff who were implementing the intervention -people you coordinated with who secured funding for the intervention			
Social Network Survey (T2/T3)				
Q#	Network Question			
1	Name all the people at your agency you collaborated with during the past year to support the (MTG/RR/SDLMI) intervention.			
1	For example, collaborators can include: -people you worked with to provide the intervention -people who provided encouragement, training or guidance about the intervention -People who provided resources needed to do the interventions -people who worked with you to support staff who were implementing the intervention -people you coordinated with who secured funding for the intervention			

Experts in each EBI will provide training regardless of randomization condition. MTG targets peer navigators (parents of children with disabilities) who will complete the 12- hour remote training on MTG modules and associated topics (e.g., boundaries, family and child safety, data collection). The research team will conduct the initial 12 h of training and active coaching/check ins once per month over a minimum of 6 and maximum of 12 months. Identified families connected to the community agency will be matched with one peer navigator who will then guide and support the caregiver through completion of the MTG modules with active coaching of the family for up to 12 sessions over 4–6 months. Family needs and preferences will guide topic selection. Active coaching will occur via Zoom, or over the phone, based on family preference. RR targets school staff on the recess yard who supervise all students, including those with ASD/NDD. Training in RR will be remote, all schools will receive a 60-to-90-min didactic training during district professional development. Active coaching (via Zoom) will occur weekly with staff at school for a minimum of 6 and up to 12 sessions during RR implementation with enrolled students. In prior studies, various school personnel (e.g., teachers, counselors, bus attendants, noontime aides, classroom assistants, and one-to-one paraeducators) have served as intervention agents. SDLMI targets school-based providers across grade levels (i.e., 6th – 12th grade) and disciplines (e.g., special education, general education). They will receive 2–4 h of remote professional development in SDLMI. Coaching will take place based on the SDLMI Facilitator Objectives that provide a road map for the facilitator. In school contexts, SDLMI instruction is implemented over the course of a semester (approximately 12 weeks) and then repeated with new goals in subsequent semesters. Practitioners will receive 12 h of remote coaching during sessions with students. We will track any unintended events (i.e., harms, consequences) as reported by site implementers. Participants will receive $25 per data collection time point (baseline, exit, and sustainment).

### Measures

#### UNITED Team Selection

##### *Roster questionnaire*

Organizational leaders will complete a roster questionnaire to identify the people at their site who in the present or future could: (1) do the proposed EBI with the target population; (2) provide implementation support for staff doing the EBI; and/or (3) make financial decisions for funding the EBI. The roster questionnaire will identify who will be included in the selection process of UNITED team members, setting the boundary for project participants at the site [38]. See Table 2.

##### *Social network survey*

People identified in the roster questionnaire will be asked to complete a social network survey where they will identify staff on the roster that would be best for three different dimensions: (1) supporting implementation of the EBI, (2) implementing the EBI and (3) allocating financial support for EBI. See Table 2.

##### *Ranked list*

Using indegree, calculated as the number of people who selected a person divided by the number of people on the roster [39], the top 1–2 people for each dimension will make up the final ranked list of recommended UNITED implementation team members at the agency/school. Most UNITED implementation teams will have two people to support and implement the EBI and one person to allocate financial support for the EBI at the school/agency level; however, some UNITED implementation teams also may have one person in the latter role at the district/system level. While ranked lists will be created for UNITED and implementation as usual sites, we will only share the ranked list with UNITED sites to support implementation team selection. To resolve situations where individuals tie with the same score, causing greater than two top scores, network betweenness scores, defined as the fraction of shortest paths that pass through a node (Linton 1979), will be used to decide who will be listed on the final ranked list. Research coordinators will meet with site leaders to select the UNITED team, using the ranked list as a guide. If the on-site leaders wish to deviate from the suggested interventionists, they will allow them to do so for the following reasons. First, local knowledge, a deep understanding of the setting, culture, and dynamics of the agency/school are of paramount value, and we wish to prioritize that. Second, the on-site leaders may be knowledgeable of key dynamics that are unobservable to the research team. For example, the local leaders may know of personality clashes or problems that will hinder implementation. Third, we know that interventions that can be adapted to local needs and conditions are more readily accepted and more effective than those which are “set in stone.” It is important to collaborate and share control with local leads to build buy-in and develop ownership over the EBI; thus, allowing them to adapt is important. We will track and report reasons provided for the deviations.

### Implementation outcomes

#### *Fidelity*

Because we are testing the effect of UNITED on use and sustainment of three EBIs that already have demonstrated effectiveness, our primary outcome measure is providers’ fidelity to each intervention. We will use the established fidelity procedures for each EBI (i.e., MTG, RR, SDLMI).

#### MTG fidelity

The fidelity of peer coach implementation of MTG will be measured through audio-recording and coding 25% of sessions, as selected by a random number generator. Following recording, a member of the research team will code the audio for fidelity using the MTG Fidelity Checklist. The MTG Fidelity Checklist records the process and procedures for each session, goal setting and review, use of MTG materials and a measure of the quality of the interaction.

#### *RR fidelity*

Fidelity (i.e. use and frequency of intervention delivery) will be measured via a 20-item self-report that captures each RR component. Use will be scored “0” for “no” and “1” for “yes” to measure whether educators used each RR component. The proportion of completed steps (completed steps/total number of RR components) will be used for analyses. Frequency of intervention delivery will be coded on a Likert-type scale from “1” (rarely) to “4” (always) for each component of RR that was used. The average quality rating across all intervention components will be used for analysis.

#### *SDLMI fidelity*

The SDLMI Fidelity Measure is completed by a trained observer or coach and targets three dimension of fidelity: adherence, quality of delivery, and participant responsiveness. It is organized into three sections: Part A – Observation Information (provides general information about the observation, including the SDLMI phase and Student Questions targeted—exposure); Part B – SDLMI Lesson Observation (provides quantitative and qualitative information on the teacher’s implementation of SDLMI core components [Student Questions, Teacher Objectives, Educational Support] – adherence, quality of delivery, participant responsiveness); and Part C – Content Observation (provides quantitative and qualitative information on teacher’s integration of SDLMI into content instruction—quality of delivery, participant responsiveness). Scores on items in each section are summed for each dimension and provide an overall fidelity index.

#### *Stages for Implementation Completion* [40] 

We will measure progress through the implementation phases using the Stages of Implementation Completion (SIC) tool, an eight-stage tool of implementation process and milestones with stages paralleling the phases of implementation (pre-implementation [exploration, preparation], implementation, sustainability). We will measure stages of implementation completion for each EBI: 1) engagement; 2) consideration of feasibility; 3) readiness planning; 4) staff hired and introduce training; 5) fidelity monitoring processes in place; 6) services and consultation to services begin; 7) model fidelity and staff competence and adherence tracked; and 8) competency. The research team will work with the agency/school to gather information to complete each stage of the SIC from recruitment through sustainment. Dates where the SIC activity was completed will be entered into the online SIC portal. We will use the implementation completion score from the SIC, along with economic analysis as part of the SIC.

#### *Cost effectiveness of interventions*

We will use the SIC tool to measure cost effectiveness of UNITED within each stage of implementation. We will track direct, indirect and ancillary costs to implement each EBI at each community site. Costs of implementation will be expressed as average cost per SIC stage for each site. However, corrections will be applied for a site that takes longer to move through a SIC stage. Regression techniques will be used to estimate risk adjusted cost functions, which can vary with such factors as the number of clients treated by a program, or the time required to move through each stage of the SIC. The dependent variable of the regression will be the logged implementation cost for each stage for each site.

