Organizational theory suggests that successful implementation is supported by systematic, planned internal “conditions,” including clearly defined roles, collaborative teams, and transparent expectations. Teams that are thoughtfully assembled, develop an implementation plan, assign roles and responsibilities, and carefully track and support implementation and sustainment in all its stages increase the quality and sustainment of implementation efforts [25, 26]. To support the creation of critical organizational “conditions,” we integrated social network implementation theories and collaborative teaming approaches to develop a multifaceted implementation strategy to facilitate implementation and sustainment of EBIs in low-resourced settings: UNITED (Using Novel Implementation Tools for Evidence-based intervention Delivery). The participating agencies and school districts and the research team have long-standing relationships, which provide an ideal natural laboratory in which to rigorously test, on a large scale, an implementation strategy that is effective for a variety of autism interventions, regardless of the setting or the age group of the intended recipient, to increase rapid uptake of effective practices to reach our most vulnerable children. We will draw on our prior work using community-partnered research to collaboratively test the implementation of three evidence-based interventions (Mind the Gap (MTG); Remaking Recess (RR); and Self-Determined Learning Model of Instruction (SDLMI). Specifically, the primary research question of this study is:Will UNITED result in improved provider fidelity (primary outcome) to each EBI in comparison to implementation as usual (IAU)? We expect that provider fidelity to an EBI (MTG, RR, SDLMI) will be higher in groups using UNITED than IAU groups.Other research questions include:Will UNITED result in better child or family outcomes of each EBI (Secondary outcomes)? We expect UNITED will result in better family empowerment for MTG, child peer social engagement for RR, and greater adolescent self-determination for SDLMI than IAU groups.Will UNITED result in greater sustainability of an EBI in the community (secondary outcome)? We expect that sustainability as measured by the Stages of Implementation Completion (SIC) will be greater for UNITED groups versus IAU.(Exploratory): Will team cohesion mediate the effect of EBI on provider fidelity? We expect that team cohesion will be greater in the UNITED condition, and team cohesion will mediate the relationship between the EBI and provider fidelity.(Exploratory): Will better implementation climate predict increase in provider fidelity to each EBI? We expect that schools/agencies with better implementation climate will have greater improvement in provider fidelity.

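### Correcting stage cost for time in stage would, if used to compare arms, remove any cost difference that UNITED causes through speed

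*Protocol article*

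**What the plan says.** The section Cost effectiveness of interventions gives the aim: "We will use the SIC tool to measure cost effectiveness of UNITED within each stage of implementation". Cost is to be summarised as an average per SIC stage for each site, with one unconditional rule: "corrections will be applied for a site that takes longer to move through a SIC stage". Neither the form of the correction nor a reference duration is given. Risk-adjusted cost functions are then to be estimated by regression, "which can vary with such factors as the number of clients treated by a program, or the time required to move through each stage". On the outcome of that regression: "The dependent variable of the regression will be the logged implementation cost for each stage for each site". No arm term is written out.

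Three other places bear on whether time in stage can depend on the arm:

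- Theoretical framework and approach describes the strategy as intended "to increase rapid uptake of effective practices to reach our most vulnerable children", and states a secondary hypothesis by arm: "We expect that sustainability as measured by the Stages of Implementation Completion (SIC) will be greater for UNITED groups versus IAU".
- Stages for Implementation Completion says the team will "gather information to complete each stage of the SIC from recruitment through sustainment", so the stages span the period before and after allocation.
- Procedures says that agencies and schools are randomised to UNITED or implementation as usual (IAU).

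**The concern.** The cost of adopting UNITED includes whatever it does to the time a site spends getting through implementation. A site that moves faster uses less staff and coaching time; a site that moves more slowly uses more. UNITED could push either way. It aims at quicker uptake, but, as the section UNITED describes, it also adds a leader meeting, a planning session, monthly team meetings and weekly check-ins. The monthly and weekly contacts recur for as long as the work lasts, so their cost grows with duration.

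For stages after randomisation, time in stage therefore lies on the path from arm to cost. Standardising cost to a common duration answers a different question: what UNITED would cost if sites in both arms moved at the same speed. An agency or district deciding whether to adopt UNITED needs the total difference. If the corrected figure is taken as the arm comparison, a saving or an extra cost that arises through time goes unreported, and the sign can reverse. The Discussion raises the prospect of a low-cost strategy, and a time-corrected contrast could not support or refute that.

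**Working it through.** The article states no cost figure, so there is nothing to reproduce. The check is a worked illustration. All cost and time values in it are assumptions; only the site numbers come from the article.

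**Inputs**

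- Sites per arm (Table 1): 10 agencies for Mind the Gap (MTG), 19 schools for Remaking Recess (RR), 21 schools for the Self-Determined Learning Model of Instruction (SDLMI).
- D: assumed UNITED/IAU cost ratio at equal stage time (direct effect), 1.0 to 1.2.
- T: assumed UNITED/IAU ratio of stage time, 0.70 to 1.25.
- b: assumed elasticity of cost with respect to time, 0.5 to 1 (1 means cost proportional to time).
- The correction is taken to standardise cost fully to a common stage time. A partial correction would remove a part of the same quantity.

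**Model**

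log(cost) = a + log(D) × arm + b × log(time in stage) + error

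- Total cost ratio by arm = D × T^b.
- Time-corrected cost ratio by arm = D.
- Part removed by the correction = T^b.

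**Results**

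| D | T | b | Total ratio | Time-corrected ratio |
|---|---|---|---|---|
| 1.10 | 0.80 | 1 | 1.10 × 0.80 = 0.88 | 1.10 |
| 1.10 | 0.80 | 0.5 | 1.10 × 0.894 = 0.98 | 1.10 |
| 1.10 | 1.25 | 1 | 1.10 × 1.25 = 1.375 | 1.10 |
| 1.10 | 1.00 | any | 1.10 | 1.10 |

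In the first row UNITED is 12% cheaper overall and is reported as 10% dearer. In the third row it is 37.5% dearer and is reported as 10% dearer. In the last row the two agree.

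Over the whole assumed range, the total ratio runs from 1.0 × 0.70 = 0.70 to 1.2 × 1.25 = 1.50, while the time-corrected ratio stays between 1.0 and 1.2.

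**Simulation check**

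Least-squares fits with and without log time as a covariate were run for the first row, with 4,000 replicates and assumed residual SDs of 0.4 (log time) and 0.3 (log cost).

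| Sites per arm | Total ratio | Time-corrected ratio |
|---|---|---|
| 10 | 0.879 | 1.098 |
| 19 | 0.880 | 1.099 |
| 21 | 0.880 | 1.102 |

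The simulation matches the algebra at all three trial sizes, so the gap is not a small-sample effect.

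**Price of leaving time out**

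Under the same assumed SDs and b = 1, the SD of log cost within arm is √(0.4² + 0.3²) = 0.5 without the correction and 0.3 with it. The interval on the log scale would then be up to about 0.5 / 0.3 = 1.67 times as wide. At b = 0.5 the SD is √(0.2² + 0.3²) = 0.36, and the ratio is about 1.2.

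**The case against.** The strongest reply is that the article never says the time-corrected cost is the arm comparison. It describes cost functions, with no arm term, and a function that shows how stage cost varies with duration is a legitimate description. The regression covariates are given only as examples. The correction itself has no stated form, and it might even mean that the per-stage average should reflect a longer duration, which would keep time-driven cost in. This stands as a limit: the bias is conditional on the corrected cost being used to compare arms. It does not dispose of the point. The section's declared purpose is the cost effectiveness of UNITED, the correction is stated without condition, and no uncorrected arm contrast is named beside it.

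A second reply is that UNITED has limited room to change stage time. Early SIC stages may precede allocation. Delivery is bounded alike in both arms: up to 12 MTG sessions over 4 to 6 months, 6 to 12 weekly RR coaching sessions, and a semester of about 12 weeks for SDLMI. The SIC hypothesis concerns sustainability and not stage duration. This narrows the point to stages after allocation and makes a large effect on time less certain. It does not make stage time independent of arm.

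A reader might infer three stronger criticisms that the article does not support:

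- **Clients treated is also on the path from UNITED to cost.** Nothing says UNITED is meant to change it. Planned numbers per site are the same in both arms (MTG 120/10 = 12 on average, RR 76/19 = 4, SDLMI 126/21 = 6), Implementation reach counts collaboration ties and not clients, and client volume may simply adjust for site size.
- **Logging cost is an error.** Log-cost regression is an accepted method, and the choice between it and a model on the cost scale is one between acceptable options.
- **Cost is related to no outcome.** The article says "We will use the implementation completion score from the SIC, along with economic analysis as part of the SIC". How the two are combined is detail that a condensed article may leave to the full plan.

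**Conclusion.** The point holds in a narrow form. For SIC stages after randomisation, a cost corrected for time in stage is a cost at equal speed. If it is the figure used to compare UNITED with IAU, it leaves out the factor T^b by which UNITED changes cost through time. In the illustration that turns a total ratio of 0.88 into 1.10, or 1.375 into 1.10.

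This rests on three conditions: the corrected cost serves as the arm contrast, UNITED changes stage time, and time drives cost. If stage time is equal by arm, the bias is zero. A reader might go further and conclude that the economic result will be wrong, or wrong in a known direction. The article does not support that: it gives no cost or duration data, and UNITED could shorten or lengthen stages. The primary fidelity analysis is not affected.

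**What to change.** State that the main economic contrast is total implementation cost per site by arm, within each intervention, not corrected for time in stage and adjusted only for factors fixed before allocation, such as the minimisation factors listed under Procedures. Keep the time-corrected cost functions as a descriptive secondary analysis, labelled as cost at equal stage time. It would help to say what form the correction takes and which SIC stages fall after allocation.

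This changes analysis wording only. Costs by site and SIC dates are already to be collected. The downside is a possibly wider interval for the main contrast; adjustment for pre-allocation factors may recover part of the lost precision.
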